### Sample size

Pilot study. There is no pre-specified sample size for the hospital pilot study. This phase will continue until agreement is reached about technical performance parameters as described below.Hospital cohort study. In the hospital setting, we consider that test specificity for mimics is more important than sensitivity such that mimics are directed away from the emergency stroke pathway whilst minimising removal of stroke patients in error. To detect a 90% (lower 95% confidence limit, 80%) diagnostic specificity for mimic identification assuming a mimic rate of 25% (i.e. 75% non-mimic or true stroke patients), one-tailed 5% type I error rate and 90% power, 167 participants (125 non-mimics) are required for the ‘per-protocol’ analysis. For validation of the hospital statistical model (combined clinical data and SMARTChip assay reading), 100 further non-mimics are needed, i.e. a further 134 patients in total. This gives a sample size of 301 (225 non-mimics). However, this target anticipates a non-mimic rate of 75% in the test population. If the mimic rate is higher, additional patients will be required. Inflating for 20% for participants who cannot feature in the ‘per-protocol’ analysis (see definition below in ‘Main hospital and ambulance study analyses’) gives an initial target sample size of 377 participants (including 281 non-mimics).Ambulance cohort study. In the pre-hospital setting, we consider that test sensitivity for mimics is more important than specificity to maximise removal of mimics from the emergency stroke pathway for service efficiency. To detect an 88% (lower 95% confidence limit, 80%) diagnostic sensitivity for mimic identification assuming a mimic rate of 40%, one-tailed 5% type I error rate and 90% power, 498 study participants (199 mimics) are required for the ‘per-protocol’ analysis (Agresti-Coull method [25]). For validation of the statistical model (combined pre-clinical data and SMARTChip assay reading), 100 further mimics are needed [26], i.e. a further 250 patients in total. This gives a sample size of 748 (299 mimics). However, this target reflects a typical FAST mimic rate of 40% amongst suspected stroke admissions. If the mimic rate is lower, additional patients will be required. Inflating for 20% of participants who cannot feature in the ‘per-protocol’ analysis (see definition below in ‘Main hospital and ambulance study analyses’) gives an initial target sample size of 935 patients (including 374 mimics).

In both the hospital and ambulance cohorts, the proportion of patients who are not eligible for inclusion in the per-protocol analysis will be monitored prospectively, and the sample size targets increased or decreased as required.

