#### Statistical analyses

Objective 1: to determine the diagnostic accuracy of SMARTChip assay WBPC readings for identification of stroke mimic conditions when a reading is obtained in the pre-hospital setting, i.e. the test is conducted on patients suspected to have stroke by ambulance staff

For the PP group, logistic regression analyses with binary diagnosis of mimic or stroke (with TIA grouped with stroke as the intended purpose of the test is to identify mimic) as the outcome variable and WBPC reading as the explanatory variable will be used to construct a receiver operating curve (ROC) for all possible test thresholds. Area under the ROC curve and optimal sensitivity, specificity, and negative and positive predictive values, will be reported with 95% confidence intervals (CI). Optimal thresholds for sensitivity and specificity will be chosen. As we consider that test sensitivity is more important than specificity in the ambulance, the optimal threshold will be chosen to maximise sensitivity for mimics, minimum 80%, but aiming to keep estimated specificity for mimics above 70%. At lower levels of sensitivity and specificity, the test is unlikely to be considered of value.

For the ITT group, sensitivity and specificity will be calculated using a two-by-two table. Patients with a verified WBPC reading will be assigned a ‘test diagnosis’ according to the optimal threshold established in the PP analysis, and patients with an unverified WBPC will be assigned a test diagnosis of stroke. If the SMARTChip was deployed in clinical practice and an unverified reading was obtained, patients would continue to be managed as suspected stroke as there would be no extra information to exclude this possibility.
2.Objective 2: to determine the diagnostic accuracy of SMARTChip assay WBPC readings for identification of stroke mimic conditions when a reading is obtained in hospital, i.e. the test is conducted on patients suspected to have stroke by hospital staff and when an ambulance test has not been undertaken

For this objective, analyses as described above for objective 1 will be conducted. In terms of optimal thresholds, as we consider that test specificity is more important than sensitivity in hospital, the optimal threshold will be chosen to maximise specificity for mimics, minimum 80%, but aiming to keep estimated sensitivity for mimics above 70%. At lower levels of specificity and sensitivity, the test is unlikely to be considered of value.

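### The stated 90% power and one-sided 5% error hold only for a cut-off fixed in advance, but objectives 1 and 2 choose the cut-off in the same per-protocol patients

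*Protocol article*

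**What the plan says.** All references are to the protocol article, Methods.

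- **Sample size, hospital.** The aim is "To detect a 90% (lower 95% confidence limit, 80%) diagnostic specificity for mimic identification assuming a mimic rate of 25" per cent, and "one-tailed 5% type I error rate and 90% power, 167 participants (125 non-mimics) are required". At a 25% mimic rate this leaves about 42 mimics.
- **Sample size, ambulance.** The aim is "To detect an 88% (lower 95% confidence limit, 80%) diagnostic sensitivity for mimic identification assuming a mimic rate of 40" per cent, with the same error and power, so that "498 study participants (199 mimics) are required". This leaves about 299 non-mimics.
- **Statistical analyses, objective 1 (ambulance).** A ROC curve over every threshold is built in the per-protocol group. From it, "the optimal threshold will be chosen to maximise sensitivity for mimics, minimum 80%, but aiming to keep estimated specificity for mimics above 70" per cent.
- **Statistical analyses, objective 2 (hospital).** The same analysis is used, but "the optimal threshold will be chosen to maximise specificity for mimics, minimum 80%, but aiming to keep estimated sensitivity for mimics above 70" per cent.
- **Intention-to-test table.** Verified readings are classified "according to the optimal threshold established in the PP analysis".
- **Study design, and objective 4 under Statistical analyses.** Phases 3 and 5 collect new data to validate the combined clinical-plus-assay models. No such check is described for the assay-only cut-off.

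**The concern.** A single-proportion sample size treats the cut-off as known. The only random quantity is then the number of correctly classified patients in the powered group. Under the planned rule the cut-off also varies from sample to sample, because it is set by the patients in the other group, and in hospital that is only about 42 mimics. This second source of variation is missing from the stated error and power.

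At stake is what a lower limit above 80% would mean. A reader of the Sample size section would take it as evidence with a 5% false-positive risk. If the claim concerns performance at an operating point with 70% on the other measure, the risk can be well above that in hospital. The intention-to-test table gives no independent check, because it reuses the threshold and most of the same patients.

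**Working it through.** **1. Reproduce the plan's numbers at a fixed cut-off.**

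The one-sided 95% Agresti-Coull lower limit is L = p̃ − z√(p̃(1−p̃)/ñ), with ñ = n + z², p̃ = (x + z²/2)/ñ and z = 1.645. For n = 125 and x = 108: ñ = 127.7, p̃ = 0.856, L = 0.805. For x = 107, L = 0.796. A pass therefore needs 108 of 125. The same calculation for n = 199 needs 169.

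| Cohort | Pass rule | Error at 80% | Power at target |
|---|---|---|---|
| Hospital, n = 125 | ≥108 | 4.2% | 92.7% (target 90%) |
| Ambulance, n = 199 | ≥169 | 4.6% | 92.2% (target 88%) |

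The smallest n from which power stays at 90% or more with an exact one-sided limit is 124 and 198, against the stated 125 and 199. The inflation also reproduces: 301/0.8 = 377 and 748/0.8 = 935. The arithmetic is sound, but it is arithmetic for a fixed cut-off.

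**2. Add the selection step.**

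Assumptions, none of them in the protocol:
- Readings are normal with equal SD in both groups, and mimics are lower.
- The 70% level on the other measure is binding.
- The true value p of the powered measure lies at the point where the other measure is 70%.

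The separation between groups is then d = Φ⁻¹(p) + Φ⁻¹(0.70). For p = 0.90, d = 1.282 + 0.524 = 1.806. For p = 0.88, d = 1.699. For p = 0.80, d = 1.366.

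In hospital the cut-off becomes the 30th lowest of 42 mimic readings (30/42 = 71.4%, while 29/42 = 69.0%). In the ambulance cohort it is the value that keeps 210 of 299 non-mimics above it (70.2%).

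The SD of the apparent powered measure is approximately √[p(1−p)/n + s²·0.7·0.3/m]. Here s is the ROC slope φ(Φ⁻¹(p))/φ(Φ⁻¹(0.70)), and m is the size of the other group.

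- Hospital, p = 0.90: √(0.0268² + (0.505 × 0.0707)²) = 0.045, against 0.027 at a fixed cut-off.
- Hospital, p = 0.80: √(0.0358² + (0.805 × 0.0707)²) = 0.067, against 0.036.
- Ambulance, p = 0.88: √(0.0230² + (0.575 × 0.0265)²) = 0.028, against 0.023.
- Ambulance, p = 0.80: √(0.0284² + (0.805 × 0.0265)²) = 0.035, against 0.028.

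**3. Simulate the rule** (20,000 or more runs per setting, Agresti-Coull limits; repeated runs agree to about one percentage point).

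| Cohort | True value at the 70% point | Limit clears 80% | 95% CI covers value at the 70% point | 95% CI covers value at the chosen cut-off |
|---|---|---|---|---|
| Hospital 125/42 | 80% | about 16% | about 70% | about 95% |
| Hospital 125/42 | 90% | about 79% | about 80% | about 95–96% |
| Ambulance 199/299 | 80% | about 9% | about 88% | about 95% |
| Ambulance 199/299 | 88% | about 87% | about 90% | about 95–96% |

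**4. Vary the assumptions.**

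- SD ratio 0.5 to 1.5: hospital pass rate 88% down to 72% at the target and 8% to 24% at 80%. Ambulance pass rate 91% down to 83% at the target and 6% to 12% at 80%.
- Value of the other measure where the powered measure equals its target, 60% to 80%: hospital pass rate about 39% to 98%; ambulance about 19% to over 99%.

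**The case against.** Four points can be made for the plan.

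**Power need not fall.** A reader might infer that choosing the threshold in the same data always costs power. The documents do not support that. They give no expected sensitivity in hospital and no expected specificity in the ambulance. If hospital sensitivity at 90% specificity is 75% or 80%, the pass rate is about 92% or 98%. This stands, so a single replacement power figure would rest on invented inputs.

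**Intervals are not generally too narrow.** A reader might infer that the reported intervals under-cover. Under the rule as simulated, ordinary intervals cover the true value at the cut-off actually chosen about 95% of the time. In the 80% scenarios, the limit clears 80% while true accuracy at the chosen cut-off is 80% or less in under 1% of runs. Under-coverage and excess error arise only when the claim concerns the target operating point. This stands. The analysis text also names no interval method, which an analysis plan may set; Agresti-Coull appears only for the ambulance sample size.

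**The criterion can fail.** A reader might infer that any test would pass, because moving the cut-off can always lift one measure. That would hold only if the 70% level were abandoned. The protocol pairs the two measures and says that a test below these levels is unlikely to be of value. The 70% level is, however, an aim for the estimate and has no power statement.

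**The numbers are right.** They are, for a fixed cut-off. That does not rescue the statement, because no cut-off is fixed and no independent check of the assay-only cut-off is described.

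**Conclusion.** The concern holds in a limited form. The 90% power and one-sided 5% error belong to a procedure with a pre-fixed cut-off. Objectives 1 and 2 describe a different procedure, so the stated operating characteristics do not apply to it. That conclusion follows from the text and needs no modelling.

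The size does depend on a model. With equal-SD normal readings, a binding 70% floor and the target at that point, the false-pass rate is about 16% in hospital and 9% in the ambulance cohort, against a nominal 5%. The pass rate at the target is about 79% and 87%, against a stated 90%. The hospital effect is larger because about 42 mimics set its cut-off. The false-pass rate stayed above 5% across the SD ratios tried. The direction of the change in power is not determined by the documents.

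**What to change.** 1. **Sample size.** State that 90% power and 5% error apply only to a pre-fixed cut-off. Add the error and power with the selection step included, as a range under stated assumptions for the other measure.
2. **Study design and Statistical analyses (objectives 1, 2 and 4).** Lock the assay-only cut-off from phases 2 and 4, and report its sensitivity and specificity in the phase 3 and 5 patients already planned. If the claim is instead about accuracy at the 70% operating point, use intervals that repeat the threshold selection, for example by bootstrap.
3. **Conclusion.** Base it on both measures together, and say so.

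**Cost.** No extra patients and a little more analysis. The power statement becomes less favourable and the intervals wider, because each validation set has only about 100 patients in the powered group. At n = 100, 87 successes are needed (L = 0.804; 86 gives 0.793). If the locked cut-off truly has 90% specificity or 88% sensitivity, the binomial chance of reaching 87 is about 88% in hospital and 69% in the ambulance cohort. The ambulance validation set would thus be a check on the estimate rather than a 90%-power test.

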### Pilot study analysis

The technology supporting the SMARTChip WBPC assay has undergone modification for use in this study. Prior to embarking on a diagnostic performance evaluation, it is necessary to confirm that key technical aspects are functioning as expected.

The following will be monitored although this is not an exhaustive list and other issues may arise that will require review:
Chip calibration failure rateBlood measurement failure rateReader software malfunctionThe range of WBPC readings being obtained is consistent with an expected range for suspected stroke from previous studies. The range will be monitored without access to clinical data.

This pilot phase will not be time or sample size limited but driven by accruing data which will determine whether any action needs to be taken. The technology and/or user training may need to be revised in an iterative way necessitating pause in patient testing whilst this is achieved. If any technology change would result in a change to the patient experience, the protocol and/or patient facing information will be amended accordingly and submitted for reapproval prior to resuming testing.

To facilitate any investigations, it may be necessary to share some clinical data collected (e.g. unblinded reference standard data) with Sarissa Biomedical and/or study investigators. Only non-identifiable information will be included.

The pilot phase will be considered completed and the study to have entered phase 2 (main hospital cohort part 1) once Sarissa Biomedical and the study investigator team are satisfied that accruing data indicates that the technology is functioning as expected. Data collected in the pilot phase which results in a pause to testing and alterations to the technology and/or training will not be used in any diagnostic performance evaluations (i.e. phase 2 onwards).

A record will be kept of all alterations made to the technology during the pilot phase.

### Main hospital and ambulance study analyses

All statistical analysis will follow quality assurance processes including taking account of relevant reporting guidelines such as STARD (Standards for the Reporting of Diagnostic Accuracy Studies) 2015 [27].

#### Visual data exploration

The data (i.e. WBPC measurements and clinical data) will be explored with visualization tools such as histograms, box and whisker plots and scattergrams to assess distribution patterns, detect missing data and outliers and look for associations and interactions between variables.

#### Analytical data exploration

Data will be explored with analytic tools. Univariate analysis will be used to investigate the linearity of the relationships between the dependent and independent variable(s). If relationship(s) are not linear, the log transformation and squared transformation will be attempted. If a transformation significantly lowers the Akaike Information Criterion (AIC), then, the variable will be transformed for use in the model selection step.

#### Analysis populations

There will be two analysis populations:
A per-protocol (PP) group will only include participants who have a verified WBPC reading, a reference standard diagnosis (i.e. not ‘unclear’) and who met the inclusion and exclusion criteria. In the emergency pre-hospital or hospital setting, it is not uncommon for initial assessment information to be later considered inaccurate as further details emerge. Study data recorded about eligibility information will be reviewed, and any tested patients who did not meet the eligibility criteria will not be included in the PP analysis. In addition, for ambulance-tested patients, data separately recorded at the hospital will be considered more accurate for age, symptom onset time and receipt of chemotherapy or radiology, and these data will be used instead of the ambulance-recorded data to determine eligibility for the PP group for these criteria.An intention-to-test (ITT) group will include participants who did and did not meet the eligibility criteria and who had either a verified or an unverified WBPC, and a reference standard diagnosis (‘unclear’ will not be included).

#### Data not contributing to analysis populations

For participants where it is not possible to assign a reference standard diagnosis (i.e. unclear), available data will be reported but will not contribute to diagnostic accuracy analyses.

Where the WBPC assay technology fails prior to the point of fingerprick sampling (i.e. calibration or buffer failure), only limited data about the test will be recorded. These data will be reported.

#### Statistical analyses

Objective 1: to determine the diagnostic accuracy of SMARTChip assay WBPC readings for identification of stroke mimic conditions when a reading is obtained in the pre-hospital setting, i.e. the test is conducted on patients suspected to have stroke by ambulance staff

For the PP group, logistic regression analyses with binary diagnosis of mimic or stroke (with TIA grouped with stroke as the intended purpose of the test is to identify mimic) as the outcome variable and WBPC reading as the explanatory variable will be used to construct a receiver operating curve (ROC) for all possible test thresholds. Area under the ROC curve and optimal sensitivity, specificity, and negative and positive predictive values, will be reported with 95% confidence intervals (CI). Optimal thresholds for sensitivity and specificity will be chosen. As we consider that test sensitivity is more important than specificity in the ambulance, the optimal threshold will be chosen to maximise sensitivity for mimics, minimum 80%, but aiming to keep estimated specificity for mimics above 70%. At lower levels of sensitivity and specificity, the test is unlikely to be considered of value.

For the ITT group, sensitivity and specificity will be calculated using a two-by-two table. Patients with a verified WBPC reading will be assigned a ‘test diagnosis’ according to the optimal threshold established in the PP analysis, and patients with an unverified WBPC will be assigned a test diagnosis of stroke. If the SMARTChip was deployed in clinical practice and an unverified reading was obtained, patients would continue to be managed as suspected stroke as there would be no extra information to exclude this possibility.
2.Objective 2: to determine the diagnostic accuracy of SMARTChip assay WBPC readings for identification of stroke mimic conditions when a reading is obtained in hospital, i.e. the test is conducted on patients suspected to have stroke by hospital staff and when an ambulance test has not been undertaken

For this objective, analyses as described above for objective 1 will be conducted. In terms of optimal thresholds, as we consider that test specificity is more important than sensitivity in hospital, the optimal threshold will be chosen to maximise specificity for mimics, minimum 80%, but aiming to keep estimated sensitivity for mimics above 70%. At lower levels of specificity and sensitivity, the test is unlikely to be considered of value.
3.Objective 3: to develop pre-hospital and hospital statistical models which combine routinely available clinical data with SMARTChip assay WBPC readings to predict a stroke mimic diagnosis

Key variables will be added to the PP models described above to determine if this could significantly increase their accuracy. Clinical variables that would be available to ambulance/hospital staff will be included to reflect those available at the point of testing. Stepwise regression with backward elimination will be used to select the clinical covariates that most influence the diagnosis of mimics in conjunction with the WBPC readings.

A stepwise variable selection procedure will be used, and only variables that significantly improve the AIC will be retained in the model. Sensitivity, specificity, ROC AUC (with confidence intervals) and threshold will be reported if a suitable model is found.
4.Objective 4: to prospectively determine the diagnostic accuracy of the statistical models from objective 3

The models derived under objective 3 will be used to predict mimic/stroke status, and sensitivity, specificity and negative and positive predictive values will be reported with 95% confidence intervals (CI) for the PP population.
5.Objective 5: to report the failure rate of the SMARTChip assay when used in the pre-hospital and hospital settings

Reasons why a SMARTChip assay measurement was attempted but not obtained will be categorised and reported. This will include the following:
Failed SMARTChip calibration or bufferFailed SMARTChip reading following successful calibration (i.e. unverified reading)User-reported clinical or operational reason for aborting the calibration or reading process

A failure rate will be calculated for pre-hospital and hospital settings.
6.Subgroup and exploratory analyses

Diagnosis accuracy calculations will be performed on a pre-specified subgroup of the PP population consisting of only those patients with a reference standard diagnosis of ‘Definite Stroke’ and ‘Definite Mimic’ (this subgroup analysis is being undertaken as it considers the highest level of clinical confidence in the diagnosis and therefore allows exploration of the SMARTChip assay performance under ideal conditions). Contingent on the results of the study, it may be important to carry out some data-driven exploratory analyses. These will be determined post hoc and reported as such.
7.Substudy analysis
Sub-study objective 1: to explore the diagnostic accuracy of two sequential SMARTChip assay WBPC readings for identification of large vessel occlusion stroke using a reading obtained in the pre-hospital setting and a second reading obtained in the hospital setting

This analysis will include only patients who have both a pre-hospital- and hospital-verified WBPC reading, a reference standard assigned and who meet all the eligibility criteria for both tests.

Logistic regression analyses with diagnosis (LVO) as the outcome, hospital WBPC reading as the explanatory variable and pre-hospital WBPC reading as a covariate will be used to construct a receiver operating curve (ROC) for all possible test thresholds. Area under the ROC curve and optimal sensitivity, specificity, and negative and positive predictive values will be reported with 95% confidence intervals (CI). As for the main in-hospital study, the optimal threshold will be chosen to maximise specificity.
b)Sub-study objective 2: to develop and retrospectively explore the diagnostic accuracy of a statistical model which combines routinely available clinical data with pre-hospital- and hospital-obtained SMARTChip WBPC readings to predict the presence of large vessel occlusion.

Key variables will be added to the model described above to determine if this could significantly increase its accuracy. Clinical variables that would be available to ambulance and/or hospital staff will be included to reflect those available at the point of testing. Multivariate logistic regression will be conducted, with diagnosis (LVO) as the outcome and pre-hospital and hospital WBPC readings along with variables considered to be of possible clinical importance (such as blood pressure, pre-hospital FAST symptoms, NIHSS) as the explanatory variables. A stepwise variable selection procedure will be used, and only variables that significantly improve the ROC AUC will be retained in the model. Sensitivity, specificity, ROC AUC (with confidence intervals) and threshold will be reported if a suitable model is found. As for the main in-hospital study, the optimal threshold will be chosen to maximise specificity.
c)Substudy subgroup and exploratory analyses

Contingent on the results of the study, it may be important to carry out some data-driven subgroup or exploratory analysis. These will be determined post hoc and reported as such.

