This early diagnostic uncertainty can therefore result in displacement of mimic patients from more appropriate local hospitals or medical specialties within a hospital, inappropriate demands on finite stroke specialist resources and delayed access to specialist care and time-critical reperfusion therapies for true stroke patients. For example, national audit in England consistently shows that 44% of confirmed stroke patients are not admitted to a HASU within 4 h of hospital arrival [11], and as it has been observed that 15–20% HASU beds are occupied by patients with mimic conditions for a typical stay of 2.5 days [12], one explanation for the inability to achieve stroke service standards is the impact of ‘false positive’ stroke admissions (i.e. mimics) upon finite specialist resources.

Blood biomarkers have potential advantages in emergency assessment but have not previously proven useful during the critical early stages of stroke as release occurs hours after onset, and complex assays are required [13–15]. However, evidence is now accumulating that detection of whole blood purine concentration (WBPC) may be able to assist with stroke versus mimic identification [16–19]. Purines are short half-life natural by-products from energy-producing metabolic pathways which accumulate rapidly during hypoxic tissue injury [16]. Hypoxia is a main pathophysiological mechanism when stroke is caused by ischaemia (due to arterial occlusion) or haemorrhage (due to associated pressure effects and vasoconstriction), but for most common mimic conditions, significant tissue hypoxia is not involved (e.g. migraine). Whilst purines are not a tissue-specific biomarker and are elevated in other hypoxic states, cerebral tissue is a particularly rich source because of its high metabolic activity and oxygen sensitivity. In the clinical context of suspected stroke, a significant WBPC difference is expected between common mimic conditions (low WBPC values) and true stroke (higher WBPC values).

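### The ROC for objectives 1 and 2 takes its direction from the fitted logistic slope, so a wrong-way assay is usually reported as about 1 minus its AUC; fixing low WBPC = mimic in advance is a free, minor improvement

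*Protocol article*

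**What the plan says.** The Background of the protocol article gives the hypothesis a direction: "a significant WBPC difference is expected between common mimic conditions (low WBPC values) and true stroke (higher WBPC values").

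Under Statistical analyses, objective 1 (ambulance, per-protocol group), mimic or stroke is the outcome of a logistic regression, and "WBPC reading as the explanatory variable will be used to construct a receiver operating curve (ROC) for all possible test thresholds". The AUC and the accuracy measures "will be reported with 95% confidence intervals (CI). Optimal thresholds for sensitivity and specificity will be chosen". Objective 2 (hospital) repeats the method: "For this objective, analyses as described above for objective 1 will be conducted". The ITT two-by-two table takes its threshold from the per-protocol analysis, and objective 3 adds clinical variables to the same per-protocol models.

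The bar for a useful test is set on sensitivity and specificity, not on the AUC. In the ambulance cohort "the optimal threshold will be chosen to maximise sensitivity for mimics, minimum 80%, but aiming to keep estimated specificity for mimics above 70" (per cent); in the hospital cohort "the optimal threshold will be chosen to maximise specificity for mimics, minimum 80%, but aiming to keep estimated sensitivity for mimics above 70" (per cent). Below those levels the article regards the test as unlikely to be of value.

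Neither the data exploration sections nor the statistical analysis section says that low WBPC is to be read as mimic when the ROC, the threshold or the ITT table is built.

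**The concern.** With a single predictor, the fitted probability of mimic rises or falls steadily with WBPC, according to the sign of the estimated slope. An ROC built on it is therefore the ROC of WBPC in whichever direction the sample happened to show. If mimics had the higher readings, the same steps would usually return an AUC above 0.5, a threshold that calls high readings mimic, and an ITT table that uses the reversed rule.

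The hypothesis would then have been contradicted, while a main reported measure looked like modest accuracy. The article offers the data-exploration transformations (log or square) as a remedy for non-linearity. They do not help here, because both preserve the order of positive readings.

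**Working it through.** **Inputs.** The ambulance design is "To detect an 88% (lower 95% confidence limit, 80%) diagnostic sensitivity for mimic identification assuming a mimic rate of 40" per cent, for which "498 study participants (199 mimics) are required" in the per-protocol analysis. Under Sample size, the hospital design needs 167 participants (125 non-mimics) at a 25% mimic rate. The article gives no AUC figure and no WBPC distribution. Normal and lognormal (log SD 1) readings, and the true AUCs below, are therefore assumptions.

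**The plan's own figures.** 199/0.40 = 497.5, so 498, leaving 498 − 199 = 299 non-mimics. 125/0.75 = 166.7, so 167, leaving 167 − 125 = 42 mimics. Exact binomial power at the stated numbers is 92.2% (199 mimics, 88% against 80%) and 92.7% (125 non-mimics, 90% against 80%). The sample sizes hold and play no part in the problem.

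**Mechanism.** In one simulated data set of 199 mimics and 299 strokes, with mimics shifted 0.5 SD upwards, the fitted slope was +0.408. The AUC of the fitted probabilities was 0.615, equal to the AUC with high WBPC read as mimic. In the hypothesised direction it was 0.385 = 1 − 0.615.

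**Closed-form approximation.** For m mimics and n strokes, take the standard error of the AUC as s = √[(m + n + 1)/(12mn)], which is exact with no signal and close to it near 0.5.

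- Hospital: s = √[168/(12 × 42 × 125)] = 0.0516.
- Ambulance: s = √[499/(12 × 199 × 299)] = 0.0264.

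If the direction follows the data, the estimate is folded about 0.5. With μ = 0.5 − true AUC and r = μ/s, the mean reported AUC is 0.5 + s√(2/π)·exp(−r²/2) + μ[1 − 2Φ(−r)]. The 95% CI lies above 0.5 with probability Φ(r − 1.96) + Φ(−r − 1.96). With the direction fixed, that probability is Φ(−1.96 − r).

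- No signal (r = 0): hospital 0.5 + 0.0516 × 0.798 = 0.541; ambulance 0.5 + 0.0264 × 0.798 = 0.521. CI above 0.5 in 5.0%, against 2.5% with the direction fixed.
- True AUC 0.45, hospital (r = 0.97): mean 0.559; CI above 0.5 in 16%, against 0.2%.
- True AUC 0.45, ambulance (r = 1.89): mean 0.551; CI above 0.5 in 47%, against less than 0.01%.

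**Simulation** (4,000 to 6,000 studies per setting, DeLong CIs, direction from the sign of the mean difference):

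| Setting | Hospital (42/125) | Ambulance (199/299) |
|---|---|---|
| No signal, normal: mean AUC | 0.541 | 0.521 |
| No signal, lognormal: mean AUC | 0.529 | 0.514 |
| True AUC 0.45, normal: mean AUC | 0.558 | 0.550 |
| same: CI above 0.5, as planned / direction fixed | 17% / 0.2% | 48% / 0% |
| True AUC 0.40, normal: mean AUC | 0.60 | 0.60 |
| same: CI above 0.5, as planned / direction fixed | about 50% / 0% | 97% / 0% |

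Across runs and distributions, the no-signal AUC exceeded 0.5 in about 73% to 94% of studies (about 93% with normal and 75% with lognormal readings). It is not always above 0.5 because the slope follows the means, whereas the AUC follows the ranks.

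**What the 80%/70% bar does.** A concave ROC through sensitivity 0.80 and specificity 0.70 has area of at least ½(0.30)(0.80) + 0.70 × (0.80 + 1)/2 = 0.12 + 0.63 = 0.75. The hospital point (0.70, 0.80) gives ½(0.20)(0.70) + 0.80 × (0.70 + 1)/2 = 0.07 + 0.68 = 0.75. A reversed assay would thus need a correct-direction AUC of about 1 − 0.75 = 0.25 or lower. No no-signal simulation reached 80% with 70%. Among reversals down to a mean correct-direction AUC of 0.36, the only ones to do so were 0.05% of hospital studies in one lognormal setting.

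**The case against.** The strongest reply is that the AUC does not decide anything. Value is judged on sensitivity and specificity, and that bar already fails a useless or weakly reversed assay. This stands, and it is the main reason the point is minor. A reader might infer that no part of the plan would count a wrong-way result as failure; that is true only of a strong reversal.

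A reader might also infer that a useless assay is bound to show an AUC above 0.5, or that its false-positive rate doubles. Neither holds. Above 0.5 is usual, not assured, and the excess is only 0.01 to 0.04. With the direction fixed, a two-sided 95% CI misses 0.5 in about 2.5% of studies on each side. Folding moves both tails to the upper side, and the total stays near 5%.

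The direction is stated in the Background, the planned box plots would show a reversal, and so would a threshold given on the WBPC scale. That is fair, but neither changes the AUC and CI that the stated method returns. Nor is a reversal likely on the article's account. It says that purines rise in other hypoxic states, but also that brain tissue is a rich source and that most common mimics lack significant hypoxia. The wrong-way values used here are scenarios, not forecasts.

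It might also be said that ROC orientation belongs in an analysis plan. The article, however, does state how the ROC is built, and that construction leaves the direction to the data. Finally, the logistic step should not be called redundant, because objective 3 builds on it.

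**Conclusion.** The point holds as a minor one. Followed as written, the analysis for objectives 1 and 2 lets the sample choose the direction of a one-directional test. It usually reports a wrong-way assay as about 1 minus its AUC and slightly inflates the AUC of a no-signal assay. The sizes rest on the per-protocol numbers implied by the Sample size section and on assumed WBPC distributions; the mechanism does not depend on the distribution.

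The documents do not support the stronger conclusion that a useless or mildly reversed assay would pass as useful. Only a correct-direction AUC of about 0.25 or lower could be expected to meet the 80%/70% bar in reverse. If the assay works as hypothesised, the reported results do not change.

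**What to change.** For objectives 1 and 2, build the ROC directly on the WBPC reading, with positive for mimic defined in advance as WBPC at or below the cut-off. Report the AUC and its CI on that scale even when it falls below 0.5. Use the same direction for the optimal threshold and the ITT two-by-two table. Label any association in the opposite direction exploratory. Keep the logistic model as the base for objective 3.

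This costs one or two sentences of analysis text. It needs no extra data, leaves the sample sizes and the 80%/70% criteria as they are, and loses nothing if the assay performs as expected.
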